|  |  |  |  |  |  |  |  |  |  |  |  |  |
| **Adverse event collection** |  | x | x | x | x | x | x | x | x | x | x | x |
|  |  |  |  |  |  |  |  |  |  |  |  |  |
| **Patient-Reported Outcome** |  |  |  |  |  |  |  |  |  |  |  |  |
| Quality of Life assessment (FACT-C) | x |  |  | x | x | x | x | x | x |  | x | x |
|  |  |  |  |  |  |  |  |  |  |  |  |  |
| **Patient survival status** |  |  |  |  |  |  |  |  |  |  | x | x |
| **Disease status** |  |  |  |  |  |  |  |  |  |  | x | x |

* Biochemistry tests include: blood urea nitrogen, creatinine, electrolytes, SGPT, SGOT, GGT, alkaline phosphatase, and bilirubin.

** Urine or serum pregnancy test for women of childbearing potential and who are sexually active must be performed at baseline and at least every month during treatment.

¥ Free T4 and TSH must be performed at baseline and at least every 8 weeks during treatment and at end of treatment or 30 days post-treatment safety follow-up.

† PD-L1 expression on Tumor and Immune Infiltrating T cells & CD4+, CD8+ and CD3+ T cell infiltration are determined on baseline biopsy, D10 and surgical resection specimen.

‡ The microsatellite instability (MSI or MMR status) is determined once on either the baseline biopsy or D10 biopsy.

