## Secondary objectives

The secondary objectives of the study are:

1. To identify the proportion of patients who remain progression free at 3 years.
2. To explore changes in PD-L1 expression and T-cell infiltration.
3. To evaluate the safety and tolerability of mFOLFOX-6/avelumab.
4. To assess the quality of life of the patients in a neoadjuvant setting with avelumab.

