    - CD4+, CD8+ and CD3+ T cell infiltration:
      - - Will be quantified in mm2 in the most abundant tumor-infiltrating area in both, the stroma and the tumor, of the baseline biopsy (continuous variable).
        - After the recruitment of around 5 patients, a cut-off value will be agreed upon and the numerical values corresponding to T cell infiltration (continuous variable) will then be classified as low or high or not applicable (categorical variable).
    - Microsatellite instability (MSI or MMR status):
      - - Will be evaluated once on either the baseline biopsy or D10 biopsy.
        - The MSI predictive markers to be assessed are: MLH-1, MSH-2, MSH-6, and PMS-2.
    1. Prior treatment (within the 30 previous days).
    2. Imaging: pelvic MRI (rectal protocol), CT or PET scan of the chest and the abdomen
    3. Patient-reported outcome: quality of life assessment using FACT-C questionnaire (Lynch BM et al., 2008):
    - The questionnaire is available in Arabic and English versions.
    - It should be completed by the patient in Arabic, or in English in case he/she does not understand Arabic.
    - Once completed, the site staff will do the data entry in the eCRF.
    - The average time to complete the questionnaire is 5 to10 minutes.
    - FACT-C is a 36-item quality-of-life questionnaire with five subscales: physical well-being (PWB), social/family well-being (SWB), emotional well-being (EWB), and functional well-being (FWB), and colorectal cancer-specific additional concerns (colorectal cancer subscale, CCS).
    - Participants rate how they have felt over the past 7 days, on a 5-point Likert scale ranging from 0 (not at all) to 4 (very much).
    - The total FACT-C score is obtained by summing individual subscale scores (PWB + EWB + SWB + FWB + CCS).
    - The overall quality-of-life score can range from 0 to 136 (two items relevant only to stoma patients are not included in the score).
    - Higher scores indicate better quality of life.
    - Each subscale has a maximum score of 28, except for the emotional well-being subscale, which has a maximum of 24.

### 8.2.2. Radiation therapy period: visits 2 to 7

The procedures to be done for 5 days from D1 to D5 during week 1 (visits 2 to 6) are as follows:

- - 1. Short-course radiation therapy:
    - **Treatment technique:**
      - Either 3D conformal or intensity-modulated radiotherapy (IMRT) treatment planning may be used on this study.

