      - Both techniques are approved, so either technique may be used.
      - Fields should be chosen to minimize dose to organs at risk (small bowel, femoral heads, and bladder).
      - Multiple beam techniques, both coplanar and non-coplanar may be used to achieve the objective.
      - CT with immobilization is required for planning.
      - Patients are to be placed in a position that best suits the technique used and ensures immobilization and displacement of normal tissues.
      - The slice thickness must be no greater than 5 mm, and the Gross Tumor Volume (GTV), Clinical Target Volume (CTV), and Planning Target Volume (PTV) must be defined on all axial CT slices.
      - Data on radiation technique and parameters should be made available for review at the beginning or completion of radiation therapy.
    - **Equipment:**
      - High energy X-rays with nominal energy of 6 MV (IMRT) or 15 MV (3D) should be used.
      - Image guidance (cone beam) should be used on daily basis.
    - **Target volume definitions.**
      - Volume definition and contouring will be done on planning CT scans.
      - Use of contrast enhanced MRI for better target delineation is encouraged.
      - GTV must include all primary tumor extent, and enlarged lymph nodes.
      - CTV includes GTV with 0.5 cm extension and all perirectal, presacral, and internal iliac lymph nodes all the way up to the sacral promontory.
      - PTV is a 1cm expansion of the CTV in all directions.
      - Adjustments of PTV anteriorly could be made to reduce incidental radiation to the bladder and bowel.
    - **Target dose:**
      - The daily dose will be 5 Gy to a total dose of 25 Gy.
      - Dose will be prescribed to an isodose surface that encompasses the PTV and allows the dose uniformity requirements of ≤5%.
      - Dose is specified in Gy to muscle.
      - Density corrections are required as all patients will be treated using CT-based planning.
    - All radiation plans should be submitted for audit to AUBMC.
    1. Adverse event collection

The procedures to be done at D10 during week 2 ± 3 days (visit 7) are as follows:

- - 1. Sigmoidoscopy
    2. Biopsy to evaluate:
    - PD-L1 expression:
      - - Will be evaluated on tumor cells and infiltrating immune T cells.
        - Will be classified as negative or positive or not applicable (categorical variable).
    - CD4+, CD8+ and CD3+ T cell infiltration:

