## Exploratory endpoints

The exploratory endpoints are:

1. Evaluation of biomarkers CD4+, CD8+ and CD3+ T cell infiltration, and changes in PD-L1 expression. This endpoint aims to demonstrate proof of concept that short-course radiation therapy up-regulates PD-L1 expression and induces immune cell infiltration.
2. Serum markers of inflammation: neutrophil/lymphocyte ratio.
3. Quality of life assessed using FACT-C questionnaire (FACT-C, English version 4 of 16 November 2007 or Arabic version 4 of 03 September 2014).

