# STATISTICS

## Statistical analysis plan

The detailed technical aspects of the statistical analyses will be provided in the SAP. The SAP will possibly take protocol amendments into account and adapt to unexpected issues raised by the trial running and/or data that affect planned analyses in the protocol.

Any deviations from the protocol regarding the description of statistical analysis in the SAP will be discussed in the study report.

Prior to locking the database, a data review meeting will be planned to review individual data and validate the SAP.

The distribution of parameters, including safety data, will be summarized using descriptive statistics according to the study variable:

- Categorical variables (binary, nominal and ordinal) will be presented by contingency tables (frequencies and percentages). Number and percentages of missing data will also be mentioned.
- Quantitative variables will be presented by their mean, standard deviation, standard error, median, quartiles and range, minimum and maximum values. The number of documented values will also be mentioned.

The primary endpoint will be presented by number and proportion of patients who achieved pCR along with the one-sided 95% confidence interval. Using Kaplan-Meier method, the median PFS will be estimated along with its 95% confidence interval. Exploratory variables will be analyzed according to their scale of measurement by using mean ± standard deviation or frequency distribution for numeric and categorical variables respectively.

Frequency distribution for AEs and SAEs will be presented per cycle and per patient. Similarly this will be done for the SAE of grade 3 or above combined.

No subgroup analysis is planned.

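### The protocol fixes a T-cell low/high cut-off agreed after about 5 patients with no rule for choosing it, and states only descriptive summaries for an endpoint meant to demonstrate a radiation effect

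*Protocol*

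**What the plan says.** **Measurement.** Under the footnote to Table 1, PD-L1 expression and CD4+, CD8+ and CD3+ infiltration "are determined on baseline biopsy, D10 and surgical resection specimen". Section 8.2.1 first treats infiltration as continuous: "Will be quantified in mm2 in the most abundant tumor-infiltrating area in both, the stroma and the tumor, of the baseline biopsy (continuous variable". Sections 8.2.2 and 8.2.5 say the same for the D10 biopsy and the surgical specimen. PD-L1 is recorded only as negative, positive or not applicable.

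**Cut-off.** Sections 8.2.1, 8.2.2 and 8.2.5 each add: "After the recruitment of around 5 patients, a cut-off value will be agreed upon and the numerical values corresponding to T cell infiltration" are then to be classified as low, high or not applicable.

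**Aim.** Section 2.2 lists as a secondary objective: "To explore changes in PD-L1 expression and T-cell infiltration". Section 10.3 goes further: "This endpoint aims to demonstrate proof of concept that short-course radiation therapy up-regulates PD-L1 expression and induces immune cell infiltration".

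**Analysis.** Section 12.1, and in the same terms the synopsis, states: "Exploratory variables will be analyzed according to their scale of measurement by using mean ± standard deviation or frequency distribution", for numeric and categorical variables respectively. The general list of summaries in 12.1 adds items such as the standard error, median and quartiles, but it too is descriptive. Section 12.1 also says: "The detailed technical aspects of the statistical analyses will be provided in the SAP". The SAP was not available for this review.

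**The concern.** Two things are fixed in the protocol body and do not serve the stated aim.

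First, the cut-off has a time (after around 5 patients) but no rule. The text names no statistic and no reference specimen. It does not say whether each of the three markers, in each of the two compartments, gets its own value. The trial is open-label, and nothing requires the threshold to be agreed without sight of the values from those patients, who are then classified by it. A SAP that followed the protocol would inherit this.

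Second, aim and analysis do not match. On the nominal schedule the D10 biopsy comes after radiation (D1 to D5) and before the first avelumab dose (D15). Baseline to D10 within a patient is therefore the comparison that addresses radiation. To demonstrate up-regulation, the trial needs an estimate of that change with its uncertainty. Mean ± SD and frequencies supply neither an interval nor a test. For PD-L1, marginal frequencies at two times do not show how many patients moved from negative to positive and how many moved back.

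At stake is whether the D10 biopsy, which Section 17 lists as a trial-specific experimental procedure, yields an interpretable answer. A shift across an arbitrary threshold could be read as up-regulation, or a real shift on the continuous scale could be missed.

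**Working it through.** **The plan's own figures.** The only design figures in the protocol concern pCR (stop at 2 or fewer of 13; reject at 10 or more of 36). Exact binomial sums give:
- early stopping probability 0.6537 at a 16% rate (stated 65.37%);
- type I error 0.0433 (within the stated 0.05);
- power 0.8008 at 35% (stated 0.80).

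These reproduce. No effect size, SD, correlation or power is given for the biomarkers, so everything below rests on assumptions.

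**Stability of the cut-off.** Assume the agreed value is the median of 5 baseline values. Its population percentile follows Beta(3,3), with 2.5% and 97.5% points of 0.147 and 0.853. The share of patients labelled high could then lie anywhere from about 85% to 15%. For the median of 36 values the approximate range is 0.342 to 0.658.

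**Information kept by a split at quantile q of a normal variable.** The formula is φ(z)²/[q(1−q)].
- q = 0.50: 0.637.
- q = 0.147 or 0.853: 0.422.

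**Gain from pairing.** The standard error of a paired mean change, relative to the same difference treated as unpaired, is √(1−ρ). It is 0.84, 0.71 and 0.55 for ρ = 0.3, 0.5 and 0.7.

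**Power.** Assume 36 pairs, ρ = 0.5, two-sided 0.05 and a shift of d SD.
- *Paired t-test, continuous:* standardised change d/√[2(1−ρ)] = 0.5/1 = 0.5, noncentrality 0.5 × √36 = 3.0, on 35 degrees of freedom.
- *Exact McNemar after dichotomising:* 20,000 simulated trials.
- *Unpaired comparison of means:* the same numbers with the pairing ignored.

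| Analysis | d = 0.5 | d = 0.8 |
|---|---|---|
| Paired, continuous | 83% | 99.7% |
| Unpaired, continuous | 56% | 92% |
| McNemar, cut at true baseline median | 39% | 79% |
| McNemar, cut at median of first 5 patients | 40% | 78% |

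At d = 0.5, ignoring the pairing costs 83 − 56 = 27 percentage points, and dichotomising costs 83 − 39 = 44. Taking the cut-off from 5 patients adds almost nothing to that on average.

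**Range.** For 30 to 44 pairs and ρ from 0.3 to 0.7:

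| Analysis | d = 0.5 | d = 0.8 |
|---|---|---|
| Paired, continuous | 61–99% | 95–100% |
| McNemar, first-5 cut-off | 28–58% | 61–93% |
| Unpaired, continuous | 49–65% | 87–96% |

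**Which pair of specimens.** Section 8.2.5 makes the tumour-area count at surgery not applicable in patients with pCR. That leaves about 36 × 0.84 = 30 evaluable at a 16% pCR rate and 36 × 0.65 = 23 at 35%. Baseline to D10 does not have this loss.

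**The case against.** The strongest reply is that nothing is lost. Each patient has a unique number, and infiltration is recorded as continuous each time, so paired continuous data will exist. The protocol does not say that these values are discarded once a low/high label is assigned. Section 12.1 keeps mean ± SD for numeric variables, so both forms may be reported. Mean ± SD could be applied to change scores, since the objective itself speaks of changes. With complete pairs, the difference between two visit means equals the mean within-patient change. The choice of a paired method is ordinary SAP content.

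Much of this stands. A reader might infer that the trial cannot show a within-patient change, or that the plan prescribes separate summaries for each visit. The text supports neither. The protocol never says per visit, never excludes change scores, and collects what a paired analysis needs. The absence of a named test would not by itself be a fault.

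A reader might also infer that the 5-patient source is what costs power. The simulation does not bear that out: the loss comes from dichotomising, and only if low/high replaces the continuous analysis. The harm of the 5-patient source is arbitrariness and poor reproducibility.

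Two things survive. The cut-off rule is written into three protocol sections, so it is not left to the SAP. And the aim in Section 10.3 is stronger than the analysis stated in Section 12.1.

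**Conclusion.** The point holds in limited form. The protocol fixes a data-dependent cut-off from about 5 patients without a selection rule or a safeguard against seeing their values. It states only descriptive summaries for an endpoint that Section 10.3 intends as a demonstration.

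The 15th-to-85th percentile range depends on assuming a median-of-5 rule, because the protocol names none. The drop from about 83% to about 40% power depends on normal data, 36 pairs, correlation 0.5, a 0.5 SD shift, and low/high being the main analysis. At 0.8 SD the drop is from 99.7% to 78%. Direction and rough size hold across the ranges shown.

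The endpoint is secondary in Section 3.2 and the synopsis and exploratory in Section 10.3. It does not enter the two-stage pCR decision, so the matter should be corrected but does not threaten the primary conclusion.

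**What to change.** **Section 12.1.** Name the within-patient D10-minus-baseline change in T-cell density, on the continuous or log scale with a 95% CI, as the main T-cell analysis. For PD-L1 negative/positive, specify a cross-tabulation of baseline against D10 within patients, with an exact McNemar test.

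**Sections 8.2.1, 8.2.2 and 8.2.5.** Replace the 5-patient cut-off with a value fixed before any result is seen, or with the median of all baseline samples. State to which marker and compartment each value applies. Use low/high for description only. The all-baseline median is also data-derived, but it follows a stated rule, is more stable, and would carry no inference.

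**Cost.** A wording change in the protocol, matching SAP text and a few lines of code. No new samples or visits are needed. If the all-baseline median is chosen, no low/high label is available during the trial.

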### 8.2.6. Follow-up visits: every 3 months after surgery

The procedures to be done every 3 months for 3 years after surgery are as follows:

- - 1. Physical examination/vital signs/weight
    2. Laboratory tests:
    - Tumor markers (CEA and CA 19-9)
    1. Concomitant medications
    2. Adverse event collection
    3. Patient-reported outcome: quality of life assessment using FACT-C questionnaire
    4. Patient survival status
    5. Disease Status

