| **DURATION OF PATIENT PARTICIPATION** | Treatment period: 16 weeks  Follow-up period: after surgery every 3 months until the study has reached Year 3  Total: 36 months |
| **TREATMENT SCHEDULE** | 1. Week 1 ± 3 days: D1-5: radiotherapy 25 Gy in 5 fractions 2. Week 2 ± 3 days: repeat biopsy 3. Week 3 (D15) ± 3 days:  - mFOLFOX-6: Oxaliplatin 85 mg/m2 in a 2-hour infusion   Leucovorin 400 mg/m² over 2 hours  48-hour infusion of fluorouracil 2,400 mg/m²   - Avelumab 10 mg/kg every 2 weeks (first administration at D15, for a total of 6 cycles)  1. Chemotherapy protocol every 2 weeks ± 3 days (weeks 3, 5, 7, 9 ,11 and 13) 2. Week 16 or 17 ± 3 days (2 to 3 weeks after last cycle of chemotherapy + avelumab): TME |
| **CLINICAL STUDY PLANNING** | Screening: no screening period  First-Patient In (FPI): 20 July 2018  First Patient First Dose - First Patient Last Dose: 10 weeks after first dose  First-Patient Last Visit: 3 years from FPI  Last-Patient In: 20 January 2020  Last Patient Last Visit: 02 May 2023  Database lock: 02 June 2023  Key statistics: 20 July 2023  Clinical Study Report approved: 20 October 2023 |
| **ENDPOINTS AND EVALUATION PARAMETERS** | Primary endpoint: proportion of patients who achieve a pathological complete response, defined as no viable tumor cells on the resected specimen.  Secondary endpoints:   1. Progression-free survival (PFS) at 3 years will be estimated with the Kaplan-Meier method and presented with the 95% confidence interval (CI). 2. Evaluation of response by obtaining Tumor Regression Grade (TRG). 3. Evaluation of biomarkers: CD4+, CD8+ and CD3+ T cell infiltration, and changes in PD-L1 expression. 4. Frequency, severity, and attribution of adverse events related to avelumab in a neoadjuvant setting. 5. Quality of life assessment using FACT-C questionnaire. |

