| **STATISTICS** | A Simon’s two-stage optimal design with a null hypothesis pCR rate ≤ 16% versus the alternative that pCR rate ≥ 35%, a type I error of 0.05 and a power of 80%. The results of the first 13 patients eligible for the primary efficacy analysis will be assessed in stage 1. If 2 or less patients achieved pCR, the study will be stopped, otherwise another 23 (eligible) patients will be added to the study (stage 2) for a total of 36 eligible for the primary efficacy analysis. If overall 10 or more patients achieved pCR, then the null hypothesis (the percentage of pCR is ≤16%) will be rejected. In total, 44 patients will be enrolled into the study considering that 15 to 20% of the patients might be not eligible for the primary analysis. .  Then, the percentage of patients achieving pCR will be calculated along with its one-sided 95% confidence interval. Also using Kaplan-Meier method, the median PFS will be estimated along with its 95% confidence interval. Exploratory variables will be analyzed according to their scale of measurement by using mean ± standard deviation or frequency distribution for numeric and categorical variables respectively.  Frequency distribution for AEs and SAEs will be presented per cycle and per patient. Similarly this will be done for the SAE of grade 3 or above combined. |

Table 1 Study flowchart

|  | **Inclusion Visit** | **Treatment Visit** | **Treatment Visit** | **Treatment Visit** | **Treatment Visit** | **Treatment Visit** | **Treatment Visit** | **Treatment Visit** | **End of Treatment Visit** | **Surgery** | **Follow-up Visit** | **End of Study Visit** |
| --- | --- | --- | --- | --- | --- | --- | --- | --- | --- | --- | --- | --- |
|  | **V1** | **V2 to V6**  **Week 1**  **D1-D5**  **± 3 days** | **V7**  **Week 2**  **D10**  **± 3 days** | **V8**  **Week 3 D15**  **± 3 days** | **V9**  **Week 5**  **± 3 days** | **V10**  **Week 7**  **± 3 days** | **V11**  **Week 9**  **± 3 days** | **V12**  **Week 11**  **± 3 days** | **V13**  **Week 13**  **± 3 days** | **V14**  **Week 16 or 17**  **± 3 days** | **Every 3 months**  **± 3 days** | **V27**  **Year 3**  **± 3 days** |
| **Informed consent** | x |  |  |  |  |  |  |  |  |  |  |  |
| **Inclusion/exclusion criteria** | x |  |  |  |  |  |  |  |  |  |  |  |
| **Disease diagnosis** | x |  |  |  |  |  |  |  |  |  |  |  |
| **Alcohol consumption and smoking history** | x |  |  |  |  |  |  |  |  |  |  |  |
| **Medical history** | x |  |  |  |  |  |  |  |  |  |  |  |

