# STUDY DESIGN

## Design

This is an open-label, single-arm multicenter and stage-2 phase II study investigating short-course radiation therapy (25 Gy in 5 fractions), followed 2 weeks later by 6 cycles of mFOLFOX-6 chemotherapy plus avelumab (10 mg/kg) given every 2 weeks in a successive manner such that mFOLFOX is administered 30 minutes after avelumab has been administered in patients with locally-advanced, potentially resectable rectal adenocarcinoma (**Figure 1**).

No screening period is planned.

All chemotherapy agents will be taken intravenously (infusion) every 2 weeks for 6 cycles during the treatment period (12 weeks), or until intolerable toxicity or withdrawal of patient’s informed consent. TME will performed 2 to 3 weeks after the last cycle of chemotherapy plus avelumab, depending on the patient’s condition and laboratory exams.

Each patient will be followed up for 3 years after surgery.

No reference therapy or placebo will be used in the trial.

Written informed consent must be obtained before any study specific medical procedure is performed.

Figure 1 Study design

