## Duration of patient participation

For each patient, the participation will last 3 years.

The study planning is as follows:

1. Screening: no screening period
2. First-Patient In (FPI): 20 July 2018
3. First Patient First - Dose First Patient Last Dose: 10 weeks after first dose
4. First-Patient Last Visit: 3 years from FPI
5. Last-Patient In: 20 January 2020
6. Last Patient Last Visit: 02 May 2023
7. Follow-up: every 3 months after the surgery
8. Database lock: 02 June 2023
9. Key statistics: 20 July 2023
10. Clinical Study Report approved: 20 October 2023

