### 8.2.7. End of study visit (last patient visit / last patient contact)

This visit and procedures also apply to patients who are prematurely withdrawn.

The last patient visit will be done at 3 years after the surgery, the visit procedures are as follows:

- - 1. Physical examination/vital signs/weight
    2. Laboratory tests:
    - Tumor markers (CEA and CA 19-9)
    1. Concomitant medications
    2. Adverse event collection
    3. Patient-reported outcome: quality of life assessment using FACT-C questionnaire
    4. Patient survival status
    5. Disease Status

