#### *Analysis of secondary efficacy variables*

Mainly, PFS will be estimated using Kaplan Meier methods. Median PFS and the PFS rate at 3 years and corresponding 95% confidence intervals will be presented. PFS will be defined for all patients regardless of their pCR as the time between the date the patient is enrolled in the study and the date the disease progression is shown on imaging or the date of death whatever is earlier and the last follow up date in the absence of disease progression or death. Patients without progression or death will be censored at the last assessment regarding progression. PFS will be analyzed for the ITT, the MITT and the PP set.

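### Visits collecting disease and survival status are timed from surgery, so a treated patient who stays on study unresected has no scheduled PFS follow-up, and ITT PFS is open to informative censoring

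*Protocol*

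**What the plan says.** The follow-up schedule starts from surgery wherever the protocol describes it. Section 3.1 says "Each patient will be followed up for 3 years after surgery", the synopsis says "Follow-up period: after surgery every 3 months until the study has reached Year 3", section 8.2.6 says "The procedures to be done every 3 months for 3 years after surgery are as follows", and section 8.2.7 says "The last patient visit will be done at 3 years after the surgery". Sections 5.3 and 8.3.1 also count the 3-monthly assessments from surgery. In Table 1, disease status and patient survival status are marked only in the follow-up and end of study columns, which come after the surgery column.

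The analysis does not depend on surgery. Section 12.4 defines the ITT set by one administration of avelumab and reserves the resection requirement for the MITT set. Section 12.8.2 says "PFS will be analyzed for the ITT, the MITT and the PP set". It starts the PFS clock at enrolment and censors patients without progression or death at their last progression assessment.

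The protocol makes surgery depend on the patient's condition and laboratory results (sections 3.1, 8.1.3 and 8.2.5). It also plans for patients outside the primary set: "44 patients will be enrolled into the study considering that 15 to 20% of the patients might be not eligible for the primary analysis".

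**The concern.** The ITT set is meant to include treated patients who never reach resection, but the visits that would supply their PFS data are counted from an event they do not have. If the schedule is followed as written, such a patient drops out of the risk set early, and for a reason that may be related to prognosis. The later part of the ITT Kaplan-Meier curve would then rest almost wholly on operated patients. It would move close to the MITT curve and lose its value as a check on it.

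This is more than a detail that an analysis plan could supply. The visit schedule decides which data exist, and assessments that were never scheduled cannot be recovered at analysis.

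**Working it through.** **Contacts open to a treated, unresected patient**

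- End of treatment visit (section 8.2.4): week 13, or within 14 days of stopping study medication. Disease status is not listed.
- Safety follow-up (section 8.3.1): to 90 days after the last avelumab dose. The sixth dose falls on day 15 + 5 × 14 = day 85, so this ends about day 175, or week 25. Disease status is not listed.
- End of study visit (sections 5.4 and 8.2.7): disease and survival status are recorded, once. Section 5.4 triggers it on withdrawal or treatment discontinuation, and 8.2.7 says "This visit and procedures also apply to patients who are prematurely withdrawn".
- Imaging: CT or PET is scheduled at inclusion only, and the pelvic MRI before surgery is optional (section 8.3.1).

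A patient who completes six cycles, is not operated on and stays on study meets neither trigger. No scheduled visit then records that patient's disease status.

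**How many patients could be affected**

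The planned enrolment reproduces: 36 / (1 − 0.18) = 43.9, so 44. Dividing by 0.85 and 0.80 gives 43 and 45, and 36 × 1.2 = 43.2 also rounds up to 44. That leaves 44 − 36 = 8 patients (8 / 44 = 18%) outside the primary set. Eight is therefore a ceiling for the unresected. The protocol states no expected rate, precision or sample size for PFS.

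**Illustration of the bias**

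Inputs:

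- 3-year PFS in resected patients, r = 50%. This borrows the historical 3-year DFS of about 50% in section 1.1.
- 3-year PFS in unresected patients, u = 10% to 90%. This is an assumption.
- Share unresected, f = 8/44, 4/44 or 2/44, taking all 44 as ITT.
- Exponential PFS in both groups. Event-free unresected patients are censored at c = 17/52 year. Both are assumptions.

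Formulas, with hazards λr = −ln(r)/3 and λu = −ln(u)/3:

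- Full follow-up: (1 − f)·r + f·u
- Large-sample Kaplan-Meier as scheduled: [(1 − f)·exp(−λr·c) + f·exp(−λu·c)] × exp(−λr·(3 − c))

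Worked case, f = 8/44 and u = 20%: λr = 0.231 and λu = 0.536. Full follow-up gives 0.818 × 0.50 + 0.182 × 0.20 = 44.5%. As scheduled, it is (0.818 × 0.927 + 0.182 × 0.839) × 0.539 = 0.911 × 0.539 = 49.1%. The difference is +4.6 points.

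| 3-year PFS, unresected | Full follow-up, 8/44 | As scheduled, 8/44 | Bias, 8/44 | Bias, 4/44 | Bias, 2/44 |
|---|---|---|---|---|---|
| 10% | 42.7% | 48.5% | +5.8 | +2.9 | +1.5 |
| 20% | 44.5% | 49.1% | +4.6 | +2.3 | +1.1 |
| 30% | 46.4% | 49.5% | +3.1 | +1.6 | +0.8 |
| 50% | 50.0% | 50.0% | 0 | 0 | 0 |
| 70% | 53.6% | 50.3% | −3.3 | −1.6 | −0.8 |
| 90% | 57.3% | 50.6% | −6.7 | −3.3 | −1.7 |

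The censoring time matters little. With 8/44 and u = 10%, the scheduled estimate is 48.9% for censoring at week 13 and 47.9% at month 6, a bias of +6.2 and +5.2 points. With r = 60%, 8/44 and u = 10 to 30%, the bias is +7.2 to +4.7 points. For scale, the standard error of a 50% proportion in 44 patients is √(0.5 × 0.5 / 44) = 7.5 points.

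**The case against.** A reader might infer that ITT PFS is definitely biased upward because unresected patients do worst. The documents do not support that. They give neither the number nor the prognosis of unresected patients. Some may decline surgery after a good clinical response, and the sign then reverses. This objection stands in full.

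A reader might also put all 8 surplus patients on this path. Enrolment is at consent and there is no screening period, so some of the 8 may never receive avelumab and fall outside ITT as well. Others may lack a baseline assessment or withdraw. Imaging progression found before planned surgery is an event, and a death learned of later still counts. This objection also stands, so 8 is only a ceiling.

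Other points stand in part:

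- Not every contact is tied to surgery, since safety follow-up is counted from the last avelumab dose. It does not list disease status.
- Section 5.3 gives each patient 3 years of participation without mentioning surgery, and "First-Patient Last Visit: 3 years from FPI" disagrees with 3 years after surgery. This sets a duration but no visits for the unresected.
- Omitting surgery could be read as discontinued treatment under section 5.4. That yields one visit.
- Censoring near month 4 is not fixed by the text. Section 12.5 censors at the last follow-up or last communication, which could be later. A later contact without a disease assessment only credits event-free time that nobody verified.
- No follow-up imaging is scheduled for anyone, and section 17 leaves it to standard care, which is also open to unresected patients. Operated patients nevertheless have a recurring visit at which disease status is recorded.

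Finally, PFS is a secondary estimate with no hypothesis test. This limits the consequence but does not close the gap.

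**Conclusion.** The gap is real: the protocol plans an ITT PFS analysis but schedules no repeated disease-status or survival-status visit for an ITT patient who stays on study without surgery. ITT 3-year PFS is therefore open to informative censoring. Upward is the likelier direction if surgery is missed through unresectability or unfitness, but that is a judgement about cause that the documents do not settle.

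Under the stated assumptions (exponential PFS, 50% at 3 years in resected patients, censoring near week 17), the bias is about +3 to +6 points with 8 of 44 unresected and 10 to 30% 3-year PFS among them. It is zero at equal prognosis and negative if they do better. With 2 of 44 it is at most about +1.5 points. Even +5.8 points is below one standard error (5.8 / 7.5 = 0.8). The pCR test, its sample size and the two-stage decision are untouched. The change is worth making because it is cheap and the lost data could not be recovered later.

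**What to change.** In sections 8.2.6 and 8.2.7 and in Table 1, state that the existing 3-monthly disease-status and survival-status visits apply to every ITT patient, whether or not surgery is done. For unresected patients, count them from a date that all have, such as enrolment (the PFS origin) or the planned surgery week. Whichever is chosen, the visits should reach at least 3 years from enrolment, because the 3-year PFS rate is read there.

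Two related texts need reconciling at the same time: the 3 years of participation in section 5.3 with the 3 years after surgery in sections 3.1 and 8.2.7, and the censoring date in section 12.5 with that in 12.8.2.

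The cost is a short wording change and follow-up visits for a few more patients. At four visits a year for 3 years that is 12 each, so at most 8 × 12 = 96 visits at the ceiling and 24 for two patients. No new procedure is needed.
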